##### ER at 90 degrees of abduction

The participant is placed in supine, trunk stabilized on the table, knees bent so that the feet are placed flat on the table. The participant’s arm is placed in 90 degrees of shoulder abduction, the elbow flexed to 90 degrees, and the wrist in neutral position. The participant’s arm is passively moved into external rotation within their pain-free range of motion 3–5 times to precondition the tissue. Then, the participant is asked to perform active ER where ‘active’ refers to the participant moving their own arm through the ROM independent of tester assistance. Active ER is measured with the Acumar™ digital inclinometer aligned between the olecranon and ulnar styloid process to measure external rotation of the glenohumeral joint. Two trials are performed with approximately 10 seconds between each trial.

##### **Forward flexion**

The participant is placed in a standardized seated position, with their back directly against the back of a straight back chair. Participants are asked to actively elevate their arm as far as they can into flexion. The Acumar™ digital inclinometer is aligned along the mid-humeral shaft with the elbow in extension and shoulder in neutral rotation by asking the subject to point their thumb towards the ceiling. Two trials are performed with approximately 10 seconds between each trial.

#### Lymphedema assessment

Geometric arm volume calculations are performed to assess lymphedema. We are calculating arm volume using circumferential measurements taken at anatomic landmarks and was determined to be a reliable and valid method of limb volume measurement [52]. The participant is seated at a table with their shoulder positioned at approximately 90° of scapular plane flexion with their straight arm resting on a table. Circumferential measurements will be taken with a thin plastic tape measure with a spring that standardizes how tightly the tape is pulled. The anatomic landmarks include the wrist to middle forearm, middle forearm to elbow, elbow to middle upper arm, and middle upper arm to a 65% mark. The 65% mark of the upper arm is 65% of the distance from the elbow (olecranon) to the shoulder tip (acromion). Calculations for limb geometric volume will be calculated using the frustum volume as described by Taylor et al. [52] The interrater reliability for this method has been found to be excellent (>0.98)^23^. A percentage difference between lymphedema limb and the uninvolved limb will be calculated to determine the amount of lymphedema. Lymphedema has been defined in recent literature as a greater than 10% difference in volume calculation for the arm compared to the uninvolved upper extremity [52].

### Participant-reported outcomes

#### Physical activity assessments

Physical activity history is assessed at baseline using an interviewer-administered physical activity questionnaire [53]. Throughout the duration of the study period, weekly 7-day physical activity logs [54] are completed by all participants and returned to the PI by mail for the Control group.

#### Dietary assessments

Dietary history is measured at baseline using the NIH-DHQ food frequency questionnaire [55]. Three-day dietary records are completed at baseline and at the completion of the study period to assess recent dietary patterns.

#### Quality of life assessments

Quality of life (QOL) is assessed using the SF-36 and FACT-B. The SF-36 is a multi-purpose, short-form health survey with 36 items used to assess physical and mental health [56]. The FACT-B (Functional Assessment of Cancer Therapy-Breast) is a breast cancer-specific questionnaire comprised of 44 items to specifically assess quality of life in breast cancer patients [57].

#### Psychosocial assessments

Depressive symptoms are assessed using the 20-item CES-D (Center for Epidemiologic Studies Depression) scale, which was designed to measure current level of depressive symptomatology [58].

#### Musculoskeletal disorders assessment

Upper limb musculoskeletal disorders is assessed using the DASH (Disabilities of the Arm, Shoulder, and Hand) and Penn Shoulder Scale (PSS). DASH is a 30-item questionnaire designed to measure physical function and symptoms of possible musculoskeletal disorders of the upper limb [59]. The PSS is a 100-point shoulder-specific self-report questionnaire consisting of 3 subscales of pain, satisfaction, and function [60].

### Tracking and monitoring of adverse events

Potential adverse events (e.g., lymphedema, pain, muscle soreness, nausea, etc.) are assessed, graded and attributed using CTCAE, v4.3 and recorded by the exercise trainer at each training session by standardized questionnaires throughout the intervention period. Adverse events reported spontaneously by the patient or observed by study nurses or physicians are similarly assessed and recorded.

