### Objectives

The primary objective of this trial is to determine the effects of a 16-week combined exercise intervention on components of metabolic syndrome (MetS) including waist circumference, blood pressure, fasting glucose, HDL, triglycerides, and glucose, compared to a usual care control group among breast cancer survivors. Secondary objectives are to determine the effects of exercise on cardiorespiratory fitness, muscle strength, body composition, quality of life, shoulder strength and range of motion (ROM), and serum levels of insulin, C-reactive protein, and glycosylated hemoglobin (HbA1c). Safety and feasibility of the supervised exercise program will be evaluated, and the sustainability of the effects will be assessed.

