**Figure 2 F2:**
[figure not shown]
Study flow.

To enhance participation rate and maintain high compliance to the intervention scheme, participants in the Control group are offered the exercise program following the study period. Participants in the Exercise group are supervised by a certified exercise specialist to ensure a tailored, personalized program is executed. The exercise intervention is based on a previously utilized program deemed safe and effective in breast cancer survivors [40].

This study was approved by the Institutional Review Board of the University of Southern California (HS-12-00141) and is registered at ClinicalTrials.gov (NCT01140282).

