### Exercise intervention

Participants in the Exercise group participate in the exercise program three times per week for 16 weeks for approximately 60 minutes per session, totaling 48 sessions. Participants train one-on-one with a Certified American College of Sports Medicine/American Cancer Society (ACSM/ACS) Cancer Exercise Trainer for each session. Aerobic exercise duration per session is increased by 5 minutes every 3-4 weeks resulting in a total of 45 minutes of aerobic exercise per session by week 16 of the intervention. The trainer documents attendance of each participant at each session. If sessions are missed, reasons are documented with make-up sessions allowable extending the program to a maximum of 18 weeks.

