### Data analysis

The main intervention effect will be assessed on the basis of a comparison between exercisers and controls as defined at randomization, regardless of exercise adherence, i.e., according to intent-to-treat principle. A 2 (group) × 2 (time) repeated measures analysis of variance (ANOVA) will be used to examine changes in MetS score and for each individual component of MetS. Stratification by type of therapy (i.e., surgery, chemotherapy, radiation) may result based on therapy regimens completed by enrolled subjects. Similar analyses as for MetS will also be performed for the secondary endpoints. Correlation analyses will be used to examine the relationship between changes of the various measured endpoints. Regression analyses regarding the repeated measurement design (T1, T2, T3) will be applied to investigate the association between exercise intervention, MetS, cardiopulmonary fitness, muscle strength, body composition, and the QOL dimensions. The influence of other potential confounding factors, such as age, clinicopathologic characteristics, and comorbidities will be explored and accounted for in the analysis. In addition, change in physical activity behavior post intervention will be explored for the follow-up time points using descriptive analysis.

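### Adverse events are solicited only at the Exercise arm's training sessions, so the control arm as described cannot supply a fair background rate for the safety objective

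*Protocol article*

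**What the plan says.** The article gives two routes by which an adverse event is captured, both under Tracking and monitoring of adverse events.

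- **Solicited.** Events are graded and attributed with CTCAE and "recorded by the exercise trainer at each training session by standardized questionnaires throughout the intervention period".
- **Unsolicited.** "Adverse events reported spontaneously by the patient or observed by study nurses or physicians are similarly assessed and recorded". This route is not tied to an arm.

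Who can reach the first route follows from other sections. Exercise intervention has the Exercise group train "three times per week for 16 weeks for approximately 60 minutes per session, totaling 48 sessions". Study design says that "participants in the Control group are offered the exercise program following the study period". The one contact with controls described between T1 and T2 is in Physical activity assessments: "weekly 7-day physical activity logs [54] are completed by all participants and returned to the PI by mail for the Control group". No adverse-event content is described for that log.

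The aim is in Objectives: "Safety and feasibility of the supervised exercise program will be evaluated". Adverse events are not an endpoint in Table 3. Data analysis sets out the group-by-time analysis for the MetS score and its components and then adds "Similar analyses as for MetS will also be performed for the secondary endpoints". It plans no between-arm analysis of adverse events.

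**The concern.** One arm is asked about symptoms at every session, and the other is heard from only if something is volunteered or noticed. Events asked about are usually recorded more often than events left to be volunteered, whatever the true rates. The examples listed (lymphedema, pain, muscle soreness, nausea) can all occur without exercise in women within 24 weeks of chemotherapy or radiation, some of them on endocrine therapy.

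An evaluation of the programme's safety therefore needs to know how often these events would have occurred anyway. The randomised control arm is the natural source of that rate, but not when its events are gathered less intensively. If the arms are later tabulated side by side, as trial reports often do, the table would lean against exercise. No analysis plan can repair this afterwards, because control events that nobody asked about are not in the data.

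**Working it through.** **Step 1. Solicited contacts per participant.** Exercise intervention gives 3 sessions per week for 16 weeks: 3 × 16 = 48, which agrees with the article's total. Make-up sessions may extend the calendar to 18 weeks.

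| | Exercise | Control |
|---|---|---|
| Questionnaire at a training session, T1 to T2 | up to 48 | 0 described |
| Volunteered, or observed by nurse or physician | yes | yes |
| Weekly activity log | yes | yes, by mail |
| DASH, PSS, shoulder strength and range of motion at T1 and T2 | yes | yes |

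The imbalance lies in the first row. The other rows are open to both arms.

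**Step 2. Size.** The documents give no adverse-event rates and no capture rates, so the size of any distortion cannot be derived from them. What follows is illustration on assumed values.

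Assume the same true risk *p* of at least one event in both arms, capture *c*E = 0.95 in Exercise, and capture *c*C in Control varied from 0.25 to 1.00. The recorded proportions are *p·c*E and *p·c*C, so the apparent risk ratio is *c*E / *c*C and does not depend on *p*.

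The chance of a nominally significant difference is taken from the normal approximation with n = 50 per arm (100 recruited, halved), two-sided 5%:

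Φ{[|d| − 1.96·√(2·p̄(1−p̄)/n)] / √[(pE(1−pE) + pC(1−pC))/n]}

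Here pE and pC are the recorded proportions, d is their difference and p̄ is their mean.

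With *p* = 0.40, the recorded proportion in Exercise is 0.40 × 0.95 = 0.38:

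| Control capture (assumed) | Recorded in Control | Apparent risk ratio | Chance of a spurious significant difference |
|---|---|---|---|
| 25% | 0.10 | 3.8 | about 92% |
| 50% | 0.20 | 1.9 | about 51% |
| 75% | 0.30 | 1.27 | about 13% |
| 100% | 0.40 | 0.95 | about 4% |

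The chance also depends on the true risk. At 50% control capture it is about 25% when *p* = 0.20 and about 79% when *p* = 0.60.

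**Step 3. What the illustration shows.** The control capture rate, which is unknown, drives the result. If controls volunteer nearly everything, little distortion remains. If they volunteer a quarter to a half, the table would mislead. The direction is against exercise whenever control capture is below Exercise capture.

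**The case against.** The strongest reply is that the article promises no comparison. Objectives sets the primary aim against usual care but words safety as an evaluation of the exercise programme, alongside feasibility, which only the Exercise arm can show. Asking at each session suits that aim. This stands: a reader might infer that a planned safety comparison is biased, and the documents do not support that. What remains is that an evaluation of the Exercise arm alone still has no background rate. Attribution under CTCAE is the stated means of separating causes, but it is a judgement made event by event and does not supply that rate.

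Second, this is a condensed article. It never states the control procedure, and the full protocol may have controls questioned, for instance at T2. This also stands as a limit: the absence of solicitation is inferred from who attends the sessions. The published rule is nevertheless specific about who asks and when, and it ties the asking to an activity that one arm does not perform.

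Other stronger readings also fail:

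- Control events are not limited to volunteered ones, since staff observation counts too.
- A higher Exercise count need not come from ascertainment alone. A true effect of exercise could add to it, and the two would be confounded.
- Upper-limb symptoms and function are not without balanced data. DASH and PSS (which has a pain subscale) are scheduled at T1 and T2 in both arms, as are dynamometer strength and range of motion. These narrow the gap. They do not grade events, count those between visits, or cover nausea or lower-limb soreness.
- Lymphedema assessment says "Geometric arm volume calculations are performed to assess lymphedema", yet Table 3 has no row for it. That does not show the measure goes uncollected: Table 3 is a summary and also omits the activity logs and dietary records. The gap is editorial.

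**Conclusion.** The point holds in limited form. As described, solicited collection reaches the Exercise arm on up to 48 occasions and the control arm on none, so control adverse-event data are not a fair background rate, and any side-by-side tabulation would tend to overstate events in the Exercise arm. The amount cannot be computed from the documents. The risk ratios of 0.95 to 3.8 rest wholly on assumed capture rates and equal true risk. The conclusion also assumes that the full protocol adds no equivalent questioning of controls. The primary endpoint is untouched and no stated analysis is wrong. This is a worthwhile low-cost improvement to how a stated objective is served.

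**What to change.** 1. Add the same short standardised adverse-event questionnaire to the weekly log in both arms. Failing that, ask it identically of both arms at T2, accepting longer recall.
2. State that any between-arm statement on adverse events uses only that common source, together with measures collected alike in both arms, such as DASH and PSS, and arm volume if it is measured in both.
3. Report events from the trainer-session questionnaires separately, as description of the Exercise arm.
4. For clarity, give the timing and arms of the arm-volume measurement, for example as a row in Table 3.

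If the full protocol already questions controls in the same way, a sentence saying so is enough.

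The cost is a short addition to an existing form, a small burden on controls, and extra work to grade and attribute events from mailed forms. One imperfection would remain: exercisers questioned at each session may be primed to write more in their logs, so the common source would reduce the imbalance without fully removing it.

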### Sample size

The primary aim is to compare changes in overall MetS scores from baseline to week 17 between the Exercise and Control groups. Since MetS has not been investigated in breast cancer survivors at the time of project initiation, we chose to calculate sample size using changes in insulin following exercise in breast cancer survivors. This project is designed to detect a treatment effect based on insulin results with 80% statistical power at a 5% level of statistical significance. Ligibel et al. assessed insulin levels before and after a 16-week exercise intervention in breast cancer survivors [40]. Using their results, a sample size of 80 participants would detect a difference in mean insulin levels of 2.6 μU/ml assuming that the common standard deviation is 4.0 μU/ml using a two group t-test with two-sided 5% level of statistical significance. Therefore, to allow for a 20% maximum withdrawal rate, 100 participants will be recruited, of whom 50 will be premenopausal and 50 postmenopausal.

### Data analysis

The main intervention effect will be assessed on the basis of a comparison between exercisers and controls as defined at randomization, regardless of exercise adherence, i.e., according to intent-to-treat principle. A 2 (group) × 2 (time) repeated measures analysis of variance (ANOVA) will be used to examine changes in MetS score and for each individual component of MetS. Stratification by type of therapy (i.e., surgery, chemotherapy, radiation) may result based on therapy regimens completed by enrolled subjects. Similar analyses as for MetS will also be performed for the secondary endpoints. Correlation analyses will be used to examine the relationship between changes of the various measured endpoints. Regression analyses regarding the repeated measurement design (T1, T2, T3) will be applied to investigate the association between exercise intervention, MetS, cardiopulmonary fitness, muscle strength, body composition, and the QOL dimensions. The influence of other potential confounding factors, such as age, clinicopathologic characteristics, and comorbidities will be explored and accounted for in the analysis. In addition, change in physical activity behavior post intervention will be explored for the follow-up time points using descriptive analysis.

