**Methods/Design:**

This study is a prospective randomized controlled trial (RCT) investigating the effects of a 16-week supervised progressive aerobic and resistance exercise training intervention on MetS in 100 breast cancer survivors. Main inclusion criteria are histologically-confirmed breast cancer stage I-III, completion of chemotherapy and/or radiation within 6 months prior to initiation of the study, sedentary, and free from musculoskeletal disorders. The primary endpoint is MetS; secondary endpoints include: muscle strength, shoulder function, cardiorespiratory fitness, body composition, bone mineral density, and QOL. Participants randomized to the Exercise group participate in 3 supervised weekly exercise sessions for 16 weeks. Participants randomized to the Control group are offered the same intervention after the 16-week period of observation.

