## Methods/Design

### Study design

This RCT targets women with stage I-III breast cancer following radiation and/or chemotherapy treatments. After obtaining written consent, participants are randomized to a supervised combined (aerobic and resistance) exercise program over 16 weeks (Exercise Group) and usual care (Control Group; see Figure 1). Endpoints are assessed at baseline (T1), after the end of the 16-week intervention (T2), and 12 weeks post-intervention (Exercise Group only; T3; see Figure 2).

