### Follow-up period

After the 16-week intervention period has ended, participants in the Exercise group are asked to return to the CERC 12 weeks later to repeat the outcome measure testing. During the 12-week period, participants are encouraged to exercise on their own without study team supervision. This can be independent or group activity and participants may seek assistance from fitness professionals as they see fit. The participants are asked to maintain weekly physical activity logs and wear a pedometer on a daily basis during this period. The purpose of this follow-up period is to determine whether the participants remain active and can maintain the benefits gained from the exercise intervention.

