Timing of an intervention is a key aspect in order to capture a time point following treatment where survivors change their lifestyle behaviors, often referred to as the “teachable moment [80]”. Currently, the optimal time to participate in an exercise intervention following breast cancer diagnosis is unknown. Capitalizing on the “teachable moment” soon after treatments by enrolling in a supervised exercise program will foster a behavioral change that will be sustainable for longer periods of time due to the positive and encouraging environment elicited through exercise. Breast cancer survivors may be more likely than other cancer survivors to harbor psychological stress of a diagnosis for longer periods of time and may have higher levels of interest in interventions [81], stressing the importance of an early intervention, supporting our inclusion of ‘early’ breast cancer survivors. ‘Early’ breast cancer survivors include women who have completed all cancer-related treatments within 0–6 months of study entry. Since many exercise trials have included survivors from 6 months- 10+ years post-treatment [82], we believe it was critical to include survivors who more recently completed treatment to capitalize on the teachable moment.

A unique component of this study is the inclusion of a 12-week follow-up period of the Exercise group after completion of the trial to measure longer-term adherence. Numerous cancer-related exercise interventions have failed to examine whether the benefits of the intervention persist following study completion despite reporting high (>80%) adherence rates [83,84]. This is an important aspect to investigate mainly since the benefits of exercise diminish due to failure of the participants to maintain a regular exercise program following study completion. Although many exercise interventions strive to instill a behavioral change to a more physically active lifestyle, there is a lack of data on post-intervention adherence. This study will determine whether the positive benefits of exercise can be maintained following a 12-week follow-up period where participants will not be actively enrolled in an investigator-led exercise intervention. Critical information in regards to diet and physical activity patterns and effects on MetS will be obtained during this period which will provide novel information for future intervention studies to achieve the goal of long-term adherence.

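### T3 is measured in the Exercise group only, so the planned T1-T2-T3 regression and the maintenance claim cannot yield an intervention effect at T3

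*Protocol article*

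**What the plan says.** - **Who is measured at T3.** Study design places the third assessment at "12 weeks post-intervention (Exercise Group only; T3; see Figure 2". Follow-up period agrees: "participants in the Exercise group are asked to return to the CERC 12 weeks later to repeat the outcome measure testing". Table 3 marks T3 for every primary and secondary endpoint without restricting it to one arm.
- **What happens to controls.** Abstract, Methods/Design: "Participants randomized to the Control group are offered the same intervention after the 16-week period of observation". Study design repeats the offer.
- **Main analysis.** Data analysis: "A 2 (group) × 2 (time) repeated measures analysis of variance (ANOVA) will be used to examine changes in MetS score", and likewise for each component, by intention to treat. Similar analyses are planned for the secondary endpoints.
- **Analysis that uses T3.** The same section goes on: "Regression analyses regarding the repeated measurement design (T1, T2, T3) will be applied to investigate the association between exercise intervention, MetS", then fitness, strength, body composition and QOL. It does not say that T3 exists in one arm only, nor how time is coded. The only follow-up analysis called descriptive concerns physical activity behaviour.
- **What T3 is meant to show.** Objectives: "the sustainability of the effects will be assessed". Follow-up period: to "determine whether the participants remain active and can maintain the benefits gained from the exercise intervention". Discussion: "This study will determine whether the positive benefits of exercise can be maintained following a 12-week follow-up period".

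**The concern.** A benefit of exercise in this trial is a difference from control. At T3 there is no control measurement, and none untouched by the programme offer is planned. Everyone observed at T3 was randomised to exercise, so whatever moves between T2 and T3 may be exercise, time or both.

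Movement without exercise is plausible on the article's own account. Women enter 0 to 24 weeks after chemotherapy or radiation and may be on endocrine therapy (Recruitment and randomization; Table 1), and the Background describes weight gain, fatigue and adverse metabolic change after treatment. Regression to the mean and selective return at T3 also have no comparator.

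At stake are the secondary regression, whose intervention coefficient could absorb a time trend, and the sustainability conclusion, which is worded more strongly than the design allows.

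**Working it through.** **1. The plan's own figure.** Inputs from Sample size: difference 2.6 and SD 4.0 μU/ml (insulin), two-sided 5%, 80% power, 20% withdrawal. The allocation ratio is not stated; 1:1 is assumed.

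- Standardised effect: 2.6/4.0 = 0.65.
- The two-group t-test needs 38.14 per arm, rounded up to 39, or 78 in all. With 40 per arm the power is 0.819.
- 80/(1 − 0.20) = 100.

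The stated 80 and 100 are reproduced. The calculation does not involve T3.

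**2. Can a T3 intervention effect be identified?** Let G = 1 for Exercise and write each cell mean as

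a + b·G + c2·[T2] + c3·[T3] + e2·G·[T2] + e3·G·[T3].

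That is six parameters. The observed cells are Exercise T1, T2, T3 and Control T1, T2: five. The design matrix has rank 5. Since G = 1 for every T3 observation, the columns [T3] and G·[T3] are identical, and only the sum c3 + e3 can be estimated. Restricted to T1 and T2, there are four cells, four parameters and rank 4, so the randomised contrast is fully identified.

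**3. What T3 does to the group term.** Suppose that exercise has no effect, that nothing changes from T1 to T2, and that both arms would drift by d SD from T2 to T3. Cells are weighted equally. The article gives no drift figure; the values of d are assumptions.

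- *T2 and T3 pooled as one post period.* Exercise change = (0 + d)/2 = 0.5d; control change = 0. False effect: 0.5d.
- *Linear time at weeks 0, 16, 28.* In the Exercise group the mean week is 44/3 = 14.67, the deviations are −14.67, 1.33 and 13.33, and their sum of squares is 394.7. Slope = 13.33d/394.7 = 0.0338d per week; control slope = 0. Over 16 weeks the false difference is 0.54d.
- *Categorical time.* e2 = (Exercise T2 − T1) − (Control T2 − T1) = 0 whatever d is. The T2 contrast is unbiased; e3 remains inestimable.

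| Assumed drift d (SD) | Pooled | Linear, at 16 weeks | Categorical, T2 contrast |
|---|---|---|---|
| 0 | 0 | 0 | 0 |
| 0.30 | 0.15 | 0.16 | 0 |
| 0.65 | 0.325 | 0.35 | 0 |

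A drift in the other direction reverses the signs.

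**4. What T3 can deliver.** With 50 × 0.8 = 40 exercisers, the 95% CI half-width for the mean T2-T3 change is t(0.975, 39)/√40 = 0.32 SD of that change. To set this beside the 0.65 SD insulin effect, take 4.0 as the SD of levels, equal at T2 and T3. Then SD of change / SD of levels = √(2(1 − ρ)), with ρ the T2-T3 correlation, which the article does not give.

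- ρ = 0.8: 0.32 × 0.632 = 0.20 SD; 0.20/0.65 = 31%.
- ρ = 0.2: 0.32 × 1.265 = 0.40 SD; 0.40/0.65 = 62%.

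**The case against.** The strongest reply is that the article is open about the one-arm follow-up and makes no between-arm claim at T3. The main effect has its own intention-to-treat analysis. The regression comes after the correlation analyses and can be read as a secondary look at how variables relate. Coding of time is commonly left to the SAP. Whether exercisers keep their T2 levels is a within-group question that T3 can describe.

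Much of this stands. The main analysis is separate, and bias in the regression depends on a coding the article does not give. But no coding supplies a control mean that is never measured, so leaving detail to the SAP does not answer the identification problem. The sentence names the exercise intervention and T3 together without a restriction, and the Discussion promises to determine maintenance of benefit, not merely to describe exercisers.

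Three stronger readings are tempting, and the article does not support them:

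- *That T3 contaminates the randomised T1-T2 comparison.* A two-group, two-time ANOVA can only use T1 and T2, because controls have no T3. A separate regression cannot alter it.
- *That a non-significant T2-T3 change will be taken as maintenance.* No such test or reading is stated, and an article may leave a numerical criterion to the full plan.
- *That an observed change of zero would be compatible with losing about half the benefit.* That share requires a T2-T3 correlation of 0.5, which is not given. It also sets an uncontrolled within-group change against a between-arm effect on insulin, which is not the MetS score. For the same reason, a retention rule based on half the between-arm effect would not repair the design.

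**Conclusion.** The concern holds for the T1-T2-T3 regression and for the maintenance claim. An intervention effect at T3 is not identifiable: five cells, six parameters, rank 5. This follows from the design and needs no assumption about the data.

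The size of any bias in the regression is conditional. It is about half of a shared T2-T3 drift under pooled or linear time, and zero under categorical time or without drift.

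T3 can support a within-group T2-T3 change with a half-width of about 0.32 SD of that change, assuming 1:1 allocation and 40 exercisers returning. It cannot show that the advantage over control persists. The main T1-T2 analysis and the sample size of 80 evaluable and 100 recruited stand as they are. The point should be corrected because it changes what the trial may conclude about sustainability, not its primary result.

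**What to change.** - **Data analysis.** State that every model estimating an intervention effect uses T1 and T2 only. State that T3 is analysed within the Exercise group alone, as mean T2-T3 change with 95% CI, labelled uncontrolled.
- **Follow-up period and Discussion.** Replace the aim of determining whether benefits are maintained by a description of the course of the measures in exercisers after supervision ends, without a concurrent control.
- **Table 3.** Mark T3 as Exercise group only.

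No visit, measurement or participant is added, and the sample size does not change. The cost is a weaker sustainability conclusion: the trial can report how exercisers fared over the 12 weeks, but not that the effect of exercise lasted.
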